**Methods:**

This randomized controlled trial will be conducted at Shanxi Provincial Hospital of Traditional Chinese Medicine. A total of 94 patients with confirmed epidermal growth factor receptor gene–mutated non–small cell lung cancer who developed rashes after EGFR-TKI treatment will be enrolled. Patients will be randomly assigned to either a JDXZ traditional Chinese medicine group (group J) or a urea ointment group (group U). The primary outcome will be the severity of the rash as assessed using the National Cancer Institute Common Terminology Criteria for Adverse Events grading. Secondary outcomes will include the WoMo (Wollenberg and Moosmann) score, numerical rating scale, Dermatology Life Quality Index scale, European Organisation for Research and Treatment of Cancer Quality of Life Questionnaire Core 30 score, median progression-free survival, and changes in the levels of fibroblast growth factor 7 and hepatocyte growth factor in the blood. Adverse reactions will be recorded throughout the study. Data will be analyzed using SPSS.

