### Study Setting

Participants will be recruited from 3 centers: Shanxi Provincial Hospital of Traditional Chinese Medicine, Shanxi Cancer Hospital, and the Second Affiliated Hospital of Shanxi Medical University. Adequate sample sizes will be obtained through various hospital departments and online platforms. Inclusion criteria will be verified, ensuring that participants have relatively complete medical records and have signed the informed consent form.

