#### Eligibility Criteria

##### Inclusion Criteria

Inclusion criteria are as follows: (1) patients diagnosed with NSCLC carrying *EGFR* gene mutations who have developed skin rashes following EGFR-TKI treatment, with rash severity graded as 1 to 3 according to the NCI-CTCAE 5.0 standards; (2) patients aged ≥18 years, with no gender restrictions, and who have a Karnofsky Performance Status score of at least 60; (3) patients with adequate hematological, hepatic, renal, and metabolic function as indicated by specific blood count and organ function parameters (white blood cells of >3 × 10^9^ per liter, absolute neutrophil count of ≥1.5 × 10^9^ per liter, platelet count of ≥100 × 10^9^ per liter, hemoglobin of >9 g/dL, serum creatinine of ≤1.5 times the upper limit of normal [ULN], bilirubin of ≤1.5 times the ULN, aspartate aminotransferase or alanine transaminase of ≤2.5 times the ULN, if liver metastases are present, AST/ALT ≤ 5 × ULN, and serum electrolyte within normal range); and (4) patients who are willing to receive the study treatment and sign the informed consent form with good compliance.

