### Interventions

In the treatment group, after EGFR-TKI treatment, patients will receive daily oral TCM-based granule treatment. The prescription consists of *A membranaceus* (30 g), *I indigotica Fort* (15 g), and *C margaritifera* (15 g). The granules will be taken twice daily, in the morning and evening, following meals for 7 days per treatment course, with 2 consecutive courses administered. In the control group, patients will apply the urea ointment to the affected areas daily, 1 to 3 times per day, with each course lasting 7 days, also for 2 consecutive courses. All medications were supplied by Shanxi Provincial Hospital of Traditional Chinese Medicine. Investigators will assess patients on days 0, 3, 7, and 14 (Table 1). During the observation period, all patients will avoid contact with irritants, particularly in areas prone to rash, and will use sunscreen daily to reduce the incidence of skin rashes.

**Table 1. T1:** Schedule of the jiedu xiaozhen granule clinical trial.

	Visit 0 (day 0; ±2 days)	Visit 1 (day 3; ±2 days)	Visit 2 (day 7; ±2 days)	Visit 3 (day 14; ±2 days)	Visit 4 (3, 6, 9, 12, 15, 18, 21, and 24 months)
Signature of the informed consent form	✓				
Inclusion and exclusion criteria for verification	✓				
Randomization grouping	✓				
Release of experimental drugs	✓				
Recovery of the experimental drugs				✓	
Basic data collection					
Demographic data	✓				
Personal history and allergy history	✓				
Study disease–related history	✓				
Evaluation of the condition and its effectiveness^a^	✓	✓	✓	✓	
History of other diseases	✓				
Concomitant medications or treatment	✓	✓	✓	✓	
Security observations					
Liver and kidney function examination	✓			✓	
Untoward effect		✓	✓	✓	
Efficacy observation					
Clinical efficacy rate (NCI-CTCAE^b^ version 5.0)	✓	✓	✓	✓	
WoMo score	✓	✓	✓	✓	
Peak pruritus NRS^c^	✓	✓	✓	✓	
DLQI^d^	✓	✓	✓	✓	
EORTC QLQ-C30^e^ scale (quality of life measurement)	✓	✓	✓	✓	
Median PFS^f^					✓
Laboratory examination (FGF7^g^ and HGF^h^ in human blood)	✓	✓		✓	
Skin histopathological examination	✓				
Evaluation of medication compliance		✓	✓	✓	
Adverse events and complications		✓	✓	✓	
Serious adverse events		✓	✓	✓	

a A systematic and comprehensive evaluation of patients with non–small cell lung cancer was conducted in accordance with the Response Evaluation Criteria in Solid Tumors (RECIST 1.1), encompassing changes in pulmonary lesions and metastatic foci, as well as indicators such as tumor marker.

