### Statistical Analysis

Data will be analyzed using SPSS Statistics for Windows (version 26.0; IBM Corp). Continuous data following a normal distribution will be expressed as means and SDs and compared within groups using a paired 2-tailed *t* test or between groups using an independent-sample 2-tailed *t* test. Data will be presented as frequencies and percentages, with chi-square tests for group comparisons and rank sum tests for ranked data. For continuous data that are not normally distributed, between-group comparisons will be performed using the Mann-Whitney *U* test, with data described as medians and IQRs. For measurements involving multiple time points, nonparametric methods such as the Friedman test will be used to ensure robust and reliable findings. A *P* value of <.05 will be considered statistically significant.

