### Sample Size

On the basis of a small-sample clinical trial, the effectiveness rate of the treatment group was 80.77% [31]. Additionally, a previous randomized controlled double-blind clinical study had a response rate of 45% [33]. Using the PASS tool (version 21), with a significance level of .05 and a power of 0.9, the total sample size was calculated as 78 participants. Accounting for a 20% dropout rate, the required sample size was determined to be 94 patients, with 47 in each group.

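### The stated tests ignore baseline rash grade, on which the ordered response categories depend; stratifying by grade alone would be a low-cost improvement

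*Protocol article*

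**What the plan says.** Under Statistical Analysis, the protocol article lists tests by data type. Frequencies and ranked data are handled "with chi-square tests for group comparisons and rank sum tests for ranked data", and "A *P* value of <.05 will be considered statistically significant". No stratum, covariate or centre term appears, and no test is tied by name to the primary outcome.

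The Inclusion Criteria admit patients "with rash severity graded as 1 to 3 according to the NCI-CTCAE 5.0 standards". Primary Outcomes defines four results:
- cured: grade 0 after treatment;
- marked effect: a fall of two or more grades;
- effective: a fall of one grade;
- ineffective: none of these.

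The first three are then pooled into one clinical efficacy rate. Table 1 has the CTCAE assessment at Visit 0, so the baseline grade is already collected. Randomization and Blinding gives a 1:1 ratio and names no stratification factor.

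**The concern.** The ordered categories are tied to baseline grade by definition, with no clinical assumption needed:

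| Baseline grade | Cured | Marked, not cured | Effective, not cured | Ineffective |
|---|---|---|---|---|
| 1 | fall of 1 | impossible | impossible | possible |
| 2 | fall of 2 | impossible | fall of 1 | possible |
| 3 | fall of 3 | fall of 2 | fall of 1 | possible |

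An unstratified rank-sum test ranks together patients who cannot reach the same categories. If one arm happens to hold more grade 1 patients, its category distribution shifts with no treatment effect. The binary efficacy rate shifts too if grade predicts response. At stake are some precision and the credibility of the result. If an imbalance appears and adjustment is chosen only then, the choice will look driven by the data.

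**Working it through.** **Inputs from the protocol article (Sample Size).** "the effectiveness rate of the treatment group was 80.77"%, against 45% in the control group, "with a significance level of .05 and a power of 0.9"; 78 patients before dropout (39 per arm) and 94 in all (47 per arm). Two-sided testing is assumed.

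**Inputs assumed, because the article gives none.** Grades 1/2/3 at 40/45/15%; centres at 60/25/15%; a range of odds ratios for response per grade.

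**Step 1: the plan's own sample size.** The pooled formula for two proportions is n = [1.96·√(2p̄(1−p̄)) + 1.2816·√(p₁(1−p₁)+p₂(1−p₂))]² / (p₁−p₂)².
- With 0.8077 and 0.45: (1.339 + 0.813)² / 0.3577² = 36.2, so 37 per arm or 74.
- With 0.80 in place of 0.8077: (1.342 + 0.818)² / 0.35² = 38.1, so 39 per arm or 78.

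Rounding the rate to 80% thus explains the stated 78. At 39 per arm the unadjusted chi-square has about 92% power for 80.77% against 45%, above the 90% target.

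**Step 2: chance imbalance in grade.** For a stratum holding 40% of patients, the standard error of the between-arm difference in share is √(2 × 0.4 × 0.6 / 47) = 0.101. A gap of 0.10 is 0.99 standard errors, so its two-sided probability is about 0.32. At 39 per arm the standard error is 0.111 and the probability 0.37.

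**Step 3: what such a gap does to the categories.** Suppose the chance of any response is the same in every grade and, as an assumption, a responder falls each further grade with probability 0.40 (JDXZ) or 0.25 (control). Averaged over arms, the cured share is then 63%, 22% and 8% for grades 1, 2 and 3. Exchanging 10 points of grade 2 for grade 1 moves the cured share by 0.10 × (63 − 22) = 4.1 points with no treatment effect. The binary rate does not move in this case, because response is equally likely from each grade.

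**Step 4: power for the binary efficacy rate**, 80.77% against 45%, 39 per arm, 40,000 simulated trials per row. Centre is not prognostic in the first row; centre log odds are spread by ±0.3 in the second and ±0.5 in the third and fourth.

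| Odds ratio per grade | Chi-square | CMH by grade | CMH by grade × centre (9 cells) |
|---|---|---|---|
| 1 | 92.5% | 91.6% | 89.3% |
| 2 | 92.2% | 92.7% | 91.0% |
| 3 | 92.5% | 94.0% | 92.9% |
| 5 | 92.3% | 95.7% | 94.9% |

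At an odds ratio of about 4.5, separate simulations gave 92% for chi-square and 95 to 96% for CMH by grade. With a smaller true effect (70% against 45%), odds ratios of 1, 2, 3 and 4.5 gave chi-square 0.62, 0.63, 0.63 and 0.61 against CMH by grade 0.61, 0.63, 0.66 and 0.69. At 70% against 45%, adding non-prognostic centres as strata gave 0.57, 0.59, 0.63 and 0.66.

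**Step 5: power for the ordered categories**, 39 per arm, 20,000 trials per row, with the depth-of-response assumption of Step 3.

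| Odds ratio per grade | Rank sum | van Elteren by grade |
|---|---|---|
| 1/3 | 84.3% | 94.6% |
| 1/2 | 86.9% | 93.6% |
| 1 | 90.2% | 93.0% |
| 2 | 93.3% | 93.6% |
| 3 | 94.5% | 94.6% |

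**Step 6: validity.** With no treatment effect, the unadjusted chi-square rejects in 4.8 to 5.4% of trials across the scenarios.

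**The case against.** The strongest reply is that nothing here is an error. Randomisation already allows for chance imbalance, and Step 6 bears this out. A reader might infer that the stated tests are invalid; they are not. The efficacy rate, which drives the sample size, counts any one-grade fall and can be reached from grades 1, 2 and 3. The definitional dependence therefore affects the ordered categories, while its effect on the binary rate depends on a prognostic strength that the article does not report. The article assigns no test to the primary outcome, a full protocol or analysis plan may specify adjustment, and the trial calls itself exploratory. All of this stands. It makes the point an improvement to a stated method and not the correction of a mistake.

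Three stronger readings are tempting but unsupported:
- **Stratifying by grade and centre together gains power.** Not in general. Nine sparse cells cost about 3 points (92.5% to 89.3%) to 5 points (0.62 to 0.57) if nothing is prognostic. They break even near an odds ratio of 3 per grade, and the documents give no evidence of an effect that strong.
- **Baseline may be graded after treatment starts.** Table 1 allows "Visit 0 (day 0; ±2 days"), and this overlaps the Visit 1 window. But eligibility, randomisation and drug release all belong to Visit 0 and move with it. The table does not show grading after drug release.
- **The conflict over centres supports the analysis claim.** Study Setting says "Participants will be recruited from 3 centers" while the Abstract says "This randomized controlled trial will be conducted at Shanxi Provincial Hospital of Traditional Chinese Medicine". That is a genuine editorial conflict, but it has no bearing on whether to stratify by grade.

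**Conclusion.** The point holds as a low-cost improvement. The stated tests are valid but leave out a variable that is already recorded and that determines which ordered categories a patient can reach.

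For the efficacy rate at the plan's own rates and 39 per arm, stratifying by grade changes power by about −1 point if grade is unrelated to response. The gain is about 0 points at an odds ratio of 2 per grade, 2 at 3 and 3 at 4.5. For the ordered categories the benefit ranges from almost nothing, when higher grades respond more, to about 10 points (84.3% to 94.6%) when they respond much less.

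Every power figure rests on the assumed grade mix and prognostic strengths; the ordered-category figures also rest on the assumed depth of response. The imbalance probability of 0.32 rests on the 40% grade 1 share and on unstratified allocation. The definitional dependence in the category table needs none of these assumptions.

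**What to change.** Amend the Statistical Analysis wording as follows:
- Compare the clinical efficacy rate by a CMH test stratified by baseline CTCAE grade (1, 2, 3), and report the Mantel-Haenszel risk difference with its 95% CI.
- Compare the ordered categories by a van Elteren test stratified by baseline grade.
- Do not cross-stratify by centre. If centre is examined, enter it as a covariate in a sensitivity analysis.

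The cost is a few lines of text and about 1 point of power if grade proves unrelated to response (1 to 2 points at 70% against 45%). No new data are needed. With 81 of 94 patients enrolled by 1 December 2025, it is late to introduce stratified allocation, so the analysis is the practical place for the change. The article keeps analysts blinded until the analysis is complete. The change is therefore credible if it is dated and approved before any outcome is examined by group.

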The dermatological adverse effects associated with *EGFR* inhibitors are transient and tend to diminish with extended treatment duration. Resolution of the rash is typically complete upon cessation of therapy, and it is seldom constrained by the dosage or duration of treatment. Xerosis and pruritus are commonly attributable to a compromised skin barrier function. The predominant therapeutic modalities used for the management of grade 1 or 2 cutaneous toxicity encompass topical treatments such as 2.5% hydrocortisone cream, topical antibiotics (including erythromycin cream, clindamycin emulsion, metronidazole cream, and tacrolimus cream), and moisturizers (such as urea cream and fusidic acid cream). For more severe cases, oral medications may be considered, such as doxycycline (100 mg twice daily) or minocycline (50‐100 mg twice daily). Oral antihistamines, including levocetirizine (5 mg daily), desloratadine (5 mg daily), diphenhydramine (25‐50 mg 3 times daily), hydroxyzine (25 mg 3 times daily), or fexofenadine (60 mg 3 times daily), can help manage pruritus. For grade 3 rashes, oral tretinoic acid (0.3‐0.5 mg per kilogram) or prednisone (0.5 mg per kilogram) may be prescribed. Gamma-aminobutyric acid receptor agonists such as gabapentin (300 mg every 8 hours) or pregabalin (50‐75 mg every 8 hours) can also be considered for symptom relief. In severe cases, the dosage of targeted drugs should be reduced according to clinical guidelines, and for grade 4 rashes, oral steroid use may be escalated, and targeted therapy should be discontinued as soon as possible. Additionally, other studies have explored alternative treatments. For example, a study by Nagase et al [22] found that rapid desensitization therapy was effective in treating severe rashes caused by molecularly targeted drugs in patients with NSCLC. Furthermore, vitamin K_1_ has shown potential in preventing rashes associated with *EGFR* inhibitors, possibly reducing both the incidence and severity of acne-like rashes [18,21].

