## Methods

### Study Design

This study is a multicenter, prospective, randomized controlled clinical trial in which participants will receive either enhanced TCM or positive control drugs. The trial will involve 94 patients with a confirmed diagnosis of *EGFR* gene mutation–positive NSCLC who developed skin rashes after using EGFR-TKIs. The participants will be divided into 2 groups: the treatment group (receiving oral JDXZ granules) and the control group (receiving topical urea ointment). Effectiveness will be assessed by comparing baseline conditions with the results at 2 weeks after treatment. Each patient will undergo 4 scheduled visits: at baseline and on days 3, 7, and 14 (Figure 1).

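### The only method named for outcomes measured at several visits, the Friedman test, has no treatment term; the between-arm day-14 comparison should be named as the result

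*Protocol article*

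**What the plan says.** The Study Design section sets the schedule: "Each patient will undergo 4 scheduled visits: at baseline and on days 3, 7, and 14". Table 1 applies it to the WoMo score, peak pruritus NRS, DLQI and QLQ-C30 (days 0, 3, 7 and 14) and to FGF7 and HGF (days 0, 3 and 14).

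Statistical Analysis has one sentence for such data: "For measurements involving multiple time points, nonparametric methods such as the Friedman test will be used to ensure robust and reliable findings". The rest of that section is organised by type of data, not by outcome:

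- Normally distributed continuous data are "compared within groups using a paired 2-tailed" t test or "between groups using an independent-sample 2-tailed" t test.
- For skewed data: "For continuous data that are not normally distributed, between-group comparisons will be performed using the Mann-Whitney" U test.
- Frequencies and ordered categories are handled "with chi-square tests for group comparisons and rank sum tests for ranked data".

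Study Design describes the effect contrast as follows: "Effectiveness will be assessed by comparing baseline conditions with the results at 2 weeks after treatment".

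**The concern.** This is a randomised comparison of JDXZ with urea, so each secondary outcome should end in an estimate of the difference between arms. The one sentence written for multi-visit outcomes points to a test that cannot give that estimate. Friedman asks whether scores change over time in the patients analysed. Applied to each arm it gives two separate answers about change. Applied to both arms together it gives one answer about overall change. Neither involves the treatment.

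Both arms are treated, and the Introduction says of these skin reactions that they "are transient and tend to diminish with extended treatment duration". If scores fall in both arms over 14 days, within-arm tests can be significant with no JDXZ benefit. They can also be significant in one arm only, by chance, when the arms do not differ. A paper that reports a significant improvement with JDXZ but not with urea would then read as evidence of an effect. Nearly all the secondary outcomes are exposed: only progression-free survival and histopathology lie outside the multi-visit group.

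**Working it through.** **1. What each named method can test**

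| Named method | Contrast | Treatment term? | Uses baseline? |
|---|---|---|---|
| Friedman | visits within patient | no | only as one of the ranked visits |
| Paired t | two visits within one arm | no | yes |
| Independent t, Mann-Whitney | arms, at one visit or on a change score | yes | not stated |
| Chi-square, rank sum | arms, for proportions or grades | yes | not stated |

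The section can therefore compare arms at day 14. It names nothing that uses the visits jointly with treatment or adjusts for baseline, and it does not rank the within-arm and between-arm results. Friedman also drops any patient with a missed visit, and the article itself allows for 20% dropout.

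**2. What within-arm testing could produce**

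The documents give no SD, correlation or trajectory for any secondary outcome, so every such input here is an assumption. Two arms with identical true means, 39 per arm (78/2, from Sample Size), four visits, equal correlation 0.5 between visits, 3,000 trials per scenario; ranges are over repeated runs:

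| Common fall by visit (SD) | Friedman significant in exactly one arm | In both arms | Between-arm t test, day 14 |
|---|---|---|---|
| 0, 0.1, 0.2, 0.4 | 48–50% | 19–21% | 5–6% |
| 0, 0.2, 0.4, 0.6 | 28–29% | 67–69% | 5–6% |

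As a check, let π be the chance that Friedman is significant within one arm. With independent, identical arms, P(exactly one) = 2π(1 − π).

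- First row: π ≈ 0.20 + 0.50/2 = 0.45, so 2 × 0.45 × 0.55 = 0.50.
- Second row: π ≈ 0.68 + 0.29/2 = 0.825, so 2 × 0.825 × 0.175 = 0.29.

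The formula cannot exceed 50%, reached at π = 0.5, and it falls towards zero for very weak or very strong trends. In a further run with a strong common trend (fall of 0.8 against a within-patient SD of 0.7), π was about 0.98 and exactly one arm was significant in 4.6% of trials. So 30% to 50% describes moderate trends only.

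**3. When JDXZ really is better**

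Adding an extra fall of 0.6 by day 14 in one arm to that strong trend (between- and within-patient SD both 0.7), Friedman was significant in both arms in about 98% of trials and so did not show the difference. The day-14 Mann-Whitney test between arms detected it in 73%.

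**4. What baseline adjustment gains**

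Assume a true day-14 difference of 0.6 SD, 39 per arm, and baseline–day-14 correlation r = 0.5.

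- Unadjusted t test: non-centrality 0.6 × √(39/2) = 2.65; power about 74%.
- ANCOVA: residual SD factor √(1 − 0.5²) = 0.866; standardised difference 0.6/0.866 = 0.693; non-centrality 0.693 × √(39/2) = 3.06; power about 86%.

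**The case against.** The strongest objection is that valid between-group tests are already named in the same section. The independent-sample t and Mann-Whitney tests compare the arms at day 14, and the roughly 5% error rate in the table belongs to a test that the plan lists. A reader might infer that the plan discards the control group for its secondary outcomes. The text does not support that.

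A reader might also infer that Study Design defines effectiveness as a within-arm change. That sentence fits the patient-level definition under Primary Outcomes, where each patient is classed by grade change from baseline and the result is a responder rate per arm. Sample Size is built on two rates, 80.77% and 45%, which implies a between-arm contrast. The sentence is loose, not wrong.

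Similarly, the Introduction's remark about reactions fading refers to extended treatment. It does not say that both arms will improve within 14 days; that is an inference, though a plausible one.

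The one-arm-only percentages describe a misreading that the document nowhere prescribes. The wording of the Friedman sentence leaves other nonparametric methods open, the trial calls itself exploratory, and detailed model specification is commonly left to an analysis plan not shown here.

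All of this stands and limits the point. It does not remove it: the article chose a method for this class of outcome, the example it chose has no treatment term, and nothing says that the between-arm tests take precedence.

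**Conclusion.** The point holds in a limited form, and the wording should be fixed. For multi-visit secondary outcomes the one method named cannot compare JDXZ with urea. The arms can be compared only visit by visit, by tests listed for continuous data in general, with no named group-by-time or baseline-adjusted analysis and no statement of which result counts. That the Friedman test lacks a treatment term is a matter of method and needs no assumption.

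The primary outcome is not affected: it is a responder proportion, covered by the chi-square or rank sum comparison. The sample size is not affected either.

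The risk of one-arm-only significance, roughly 30% to 50% with moderate equal improvement, depends on the assumed correlation and trends and on analysts contrasting two within-arm p-values. The gain from baseline adjustment, about 74% to 86% power, depends on the assumed 0.6 SD difference and r = 0.5.

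**What to change.** In Statistical Analysis, replace the Friedman sentence. For each repeated continuous outcome, fit a mixed model for repeated measures to the post-baseline visits, with treatment, visit, treatment-by-visit, and baseline value by visit. State that the day-14 between-group difference with its 95% CI is the result for that outcome. If a distribution is badly skewed, use rank ANCOVA at day 14 adjusted for baseline. Because a rank analysis gives no difference on the original scale, add a Hodges-Lehmann estimate of the day-14 shift with its 95% CI. Label Friedman and paired tests as descriptive, not as evidence of a treatment effect.

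In Study Design, say that change from baseline to day 14 is compared between groups.

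The cost is two wording changes and a little programming; SPSS, the named package, has a mixed-model procedure. No new data are needed. With 81 of 94 patients enrolled by December 1, 2025 and completion estimated for January 31, 2026, the change should be approved and dated before the analysts learn the group codes.
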